### Personal education tools

We prepared three types of tools: a workbook, a booklet on family empowerment as a sub-textbook, and an online meeting system manual. The textbook, booklet, and online meeting system manual are distributed to the program participants. The online meeting manual, which describes the use of Zoom® is distributed and made available online. The textbook was printed in color, and innovations were added, such as large font and large sheets of paper for homework, to ensure that the participants could comfortably participate in the program. A certificate of completion was inserted at the end of the textbook, and after participating in the last session, a PDF copy of the certificate of completion was emailed to the participants, with the aim of improving self-compassion. The booklet is used as a tool to promote awareness of family empowerment. An explanation of the three levels of family empowerment and explanations of each item were provided with illustrations, ensuring that the participants can easily refer to the content during the program and can link the content to family empowerment and their situations.

### Facilitators

The lead facilitators who oversee the entire program are university faculty members who have specialized in pediatric or family nursing with a career of about 10 years. Furthermore, when the participants are separated into smaller groups, the facilitators in charge of the smaller groups are people with deep ties to children with disabilities and their family, such as specialists routinely involved with these children, family members, or parties raising these children. A facilitation book is created to standardize the program. This book follows the textbook, describing in detail, the time needed for work within the program and important points to note, to ensure that the quality of progress is sustained among the facilitators.

### Data collection method

In order to evaluate the effectiveness of this program, data is collected from participants through an online survey. Participants are invited to complete online questionnaires that assess their family empowerment, caregiver burden, self-reported capability to use social resources, self-compassion, and quality of life. A survey request email is sent to the participants regarding the online survey at the times described below, and one or more reminders are sent to those who do not respond. Participants are requested to cooperate in the survey regardless of their program attendance. For example, even if a participant does not attend any sessions, they are asked to complete the survey.

The online survey is conducted at the following three time points. After the participants apply for the program and are allocated to either the early or delayed group, they are notified of their attendance month (from July to December). At the time, participants are not informed if they are in the early or delayed group; they are simply notified of their attendance month to prevent response bias based on the participant’s impression of their allocated group. Thereafter, the initial evaluation (Time 1 [T1]) is conducted before the early group starts the first session. For the early group, this corresponded roughly to a week before attending the program. The post-intervention evaluation (Time 2 [T2]) is conducted immediately (within 1 week) after the early group completed all four sessions in the program (4 weeks). The follow-up evaluation (Time 3 [T3]) is conducted 4 weeks after the post-intervention evaluation. The timings are the same for the delayed group; however, it begins the program precisely 4 weeks after the early group does. That is, the delayed group completes the evaluation for T1 roughly 5 weeks before attending the program, T2 immediately before attending the program, and T3 immediately after completing the course.

The response information is collected in the online survey system. Participants are allocated identity documents (IDs) that are linked to the response information, and every response of each participant from T1 to T3 can be linked. If there are multiple responses from the same person at the same time (duplications), it is assumed that it is because the respondent wished to correct their answer; hence, the later response is adopted. The data collected in the online survey system are backed up fortnightly. Once all the participants complete the follow-up evaluations, the data are downloaded from the system and stored as primary raw data.

### Outcomes and measurement methods

### Feasibility outcomes

The primary outcome of this study is to determine the feasibility of a future study. Feasibility will be assessed through recruitment and retention rates assessed at pre-intervention through to T3. Acceptability will be assessed through participant feedback on satisfaction and adverse events with the conduct of the intervention collected at T3.

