In addition to these outcomes, the following questions are asked about basic attributes. At T1, the participants are asked about their relationship (from the child’s perspective), age (in 10-year increments), marital status, cohabitation status with partner, highest level of education, occupation, household income, and family members living in the same household. At T1, the following questions are asked about the child’s attributes: gender, age, name of the diagnosis, age at diagnosis, school attendance history, condition of disability, and required care. At T2 and T3, the respondents are asked if there are any changes in these circumstances and are asked to provide details if there are any. To ensure that the responses are not compulsory, the respondents are given the option of, “No response” and the online survey system is arranged so that respondents could progress to the next page without answering some or all questions.

The respondents are asked the following questions in the questionnaire to evaluate the process after attending the program and four weeks later: How did you feel after attending the program? Did you tell your family about the content of the program and the information you learned? Would you recommend the program to your friends? How can the program be expanded? They are asked their opinion about the program (age of their child when they attended the program, number of sessions, days the sessions are held, the length of the program, and the necessity of childcare).

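### Satisfaction and adverse events are fixed at T3, which falls 4–5 weeks after the last session in the early group but 0–1 week after it in the delayed group, and the article's other timing statement conflicts with this

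*Protocol article*

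**What the plan says.** Three places in the protocol article bear on when participants report on the programme.

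- **Feasibility outcomes.** Acceptability rests on "participant feedback on satisfaction and adverse events with the conduct of the intervention collected at T3". One time point is given, and it is the same for both groups.
- **Data collection method.** "The online survey is conducted at the following three time points". T2 comes within a week of the early group's last session. For T3: "The follow-up evaluation (Time 3 [T3]) is conducted 4 weeks after the post-intervention evaluation". Of the delayed group the article says "it begins the program precisely 4 weeks after the early group does", so that its surveys fall as follows: "T2 immediately before attending the program, and T3 immediately after completing the course".
- **Main outcome (closing paragraphs on the questionnaire).** Further questions serve to "evaluate the process after attending the program and four weeks later". Those listed cover how the participant felt, whether the content was passed on to the family, whether the programme would be recommended, how it could be expanded, and opinions on its format. Adverse events are not among them.

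The Data analysis section names feasibility as the primary outcome and says that it will be assessed with descriptive statistics. For acceptability it refers to satisfaction, opinions and free responses.

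**The concern.** T3 is one calendar point, but the groups reach it at different distances from the programme. For the early group it is a follow-up survey; for the delayed group it is the end-of-course survey. Asking about satisfaction and adverse events only then puts fresh impressions and month-old recollections into one summary.

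The questionnaire description does not settle the matter. It sets a different schedule, and half of that schedule cannot be carried out for the delayed group. It also leaves T3 as the only time point named for adverse events.

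At stake is the reading of one component of the primary feasibility outcome. Minor or short-lived problems with the sessions may be recalled less completely after a month than after a few days, and satisfaction may shift over the same interval. A reader of a pooled T3 figure could not tell which period it describes.

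**Working it through.** **Inputs**

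- Four weekly sessions (Intervention methods). Taking the first early session as week 0, early sessions fall at weeks 0, 1, 2 and 3.
- T1 is roughly a week before the early start, so about week −1 (Data collection method).
- T2 is 0–1 week after the last early session: 3 + 0 to 3 + 1 = week 3–4.
- T3 is T2 + 4 = week 7–8.
- The delayed group starts at week 0 + 4 = 4, so its sessions fall at weeks 4, 5, 6 and 7.

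**Reproducing the article's own description**

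- Delayed T1 to programme start: 4 − (−1) = 5 weeks. The article says roughly 5 weeks.
- Delayed T2 to programme start: 4 − 4 to 4 − 3 = 0–1 week. The article says immediately before.
- Delayed last session to T3: 7 − 7 to 8 − 7 = 0–1 week. The article says immediately after.

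The calendar is consistent with itself.

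**Time from last session to each survey**

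| Survey | Early group (last session week 3) | Delayed group (last session week 7) |
|---|---|---|
| T2 (week 3–4) | 0–1 week | programme not yet started |
| T3 (week 7–8) | 7 − 3 to 8 − 3 = 4–5 weeks | 0–1 week |

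At T3 the gap differs by 7 − 3 = 4 weeks, wherever T2 falls in its one-week window. Counting back to the first session, recall reaches 7–8 weeks in the early group (7 − 0 to 8 − 0) and 3–4 weeks in the delayed group (7 − 4 to 8 − 4).

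**Setting the two schedules side by side**

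- *Feasibility outcomes (T3 only):* the lag is 4–5 weeks in one group and 0–1 week in the other.
- *Questionnaire description, first point (after the programme):* early T2 and delayed T3, both 0–1 week. The timing is matched.
- *Questionnaire description, second point (four weeks later):* early T3 exists. For the delayed group this would be about week 7 + 4 = 11 to 8 + 4 = 12. The last of the three surveys is at week 7–8, so no such survey exists.

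The two schedules therefore disagree about whether the early group is asked at T2, and the second cannot be completed by the delayed group within T1–T3. For adverse events only the T3 statement applies.

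**The case against.** The strongest reply is that the questionnaire description already supplies what is wanted. Early T2 and delayed T3 both fall within about a week of the last session, so satisfaction-type feedback can be summarised at equal lag. That stands for the process questions. It does not remove the conflict with the T3-only statement, and it does not reach adverse events, which are mentioned only with T3. A condensed article need not list every item, so the lack of an adverse-event question in that list does not prove that none is asked at T2. The point rests instead on the time point the article does state.

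It is also fair to say that nothing inferential depends on this. Acceptability is to be described, and no comparison of satisfaction or adverse events between groups is planned. The effect is on interpretation.

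A reader might infer two stronger things. Neither is supported.

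- *That dropouts are never asked.* Data collection method says participants are surveyed whether or not they attend, including those who attend no session, and non-responders get one or more reminders. People who stop attending are therefore still sent T3. What is lost is survey non-response and formal withdrawal, which Ethical considerations allows at any time without a reason. The 10% dropout assumption under Sample size cannot be read as people who were not contacted.
- *That harm is understated by some large factor.* The documents give no adverse-event rate and no link between adverse events and non-response. Any such factor would only restate the assumptions put in.

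**Conclusion.** The point holds as a problem of timing and internal consistency. As written, T3 feedback on satisfaction and adverse events is given 4–5 weeks after the last session by the early group and 0–1 week after it by the delayed group, a constant difference of four weeks. The two statements of when participants give feedback disagree, and the four-week process questions have no survey to sit in for the delayed group. T3 is the only stated collection point for adverse events, so early-group members who answer T2 but not T3 would contribute nothing on them although they were surveyed just after the programme.

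This assumes that sessions run weekly as described and that T2 falls anywhere in its one-week window. It does not depend on the sample size, the dropout rate or any assumed event rate. The size of any recall effect cannot be estimated from the documents. The consequence is an ambiguous descriptive result within the primary feasibility outcome. That is worth correcting, but it does not threaten the efficacy analysis.

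**What to change.** 1. Reconcile Feasibility outcomes, Data collection method and the questionnaire description at the end of the outcomes section, so that a single schedule for participant feedback applies.
2. Collect satisfaction and adverse events at each group's first post-programme survey, T2 for the early group and T3 for the delayed group. Define this as the acceptability and adverse-event outcome, and pool the groups only at this matched point.
3. Report the early group's T3 answers separately as four-week follow-up, and state that the four-week questions apply to the early group only.

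This keeps adverse-event information from early-group members who answer T2 but not T3. The cost is a few extra items in a survey the early group already receives. Placing them after the outcome scales avoids influencing the T2 Family Empowerment Scale answers. If the surveys have already gone out with adverse events at T3 only, the fallback is to report those answers by group with the lag stated, without pooling.

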### Main outcome

The main outcome is family empowerment. Family empowerment is measured each time at T1–T3 using the Japanese version of the Family Empowerment Scale (FES) [22]. FES evaluates whether a family is able to control its family life while collaborating with others, addressing the three levels of “Family (internal) relationships (FA),” “Relationships with service systems (SS),” and “Involvement with community (SP).” Responses to 34 items on a 5-point scale are summed, and the results are obtained as the total score and three subscale scores. The higher the score, the higher the level of family empowerment. In case of missing responses, if more than half of items are answered, the missing data are supplemented by averaging the answered items.

Secondary outcomes are caregiver burden, self-reported capability to use social resources, self-compassion, and QOL of primary caregivers. Caregiver burden is measured using the short form of the Japanese version of the Zarit Caregiver Burden Interview (J-ZBI-8) [23]. The ZBI-8 evaluates caregiver burden, including physical and mental burden and constraints on social activities. Eight items are answered on a 5-point scale, and the caregiver burden score is obtained as the total score by summing the responses. The higher the score, the greater the caregiver burden. These outcomes are evaluated each time at T1–T3. In case of missing responses, if more than half of items are answered, the missing data are supplemented by averaging the answered items.

It has been shown that parents raising children with disabilities have sleep disturbances, which creates a burden for parents [24]. Therefore, we added two items on sleep-related issues. One question inquires whether the parent gets up during the night to care for the child: “How often do you need to get up during the night to care for your child with disabilities?” The respondents chose “every night,” “several nights a week,” “several nights a month,” “never,” and “other (state specific information).” The other question asks about the average hours of sleep per day. These items are asked each time at T1–T3.

Two original items are created regarding the use of social resources based on discussions among the researchers in our previous study [12]. The first question is asked each time at T1–T3: “Do you feel you can use social resources, properly?” and respondents can select from “I often use social resources,” “I sometimes use social resources,” “I do not use social resources very often,” and “I never use social resources.” The second question, asked at T2 and T3, is “Do you feel that you are now more able to properly use social resources compared to when you answered the previous questionnaire?” and the respondents selected “can no longer use social resources,” “cannot use social resources very much,” “unchanged,” “can use social resources slightly more,” or “can use social resources very often.” The survey also inquires about the participants’ actual use of social resources (actual use volume and frequency) as basic attributes.

Self-compassion is measured each time at T1–T3 using the short form of the Japanese version of the Self-Compassion Scale (SCS) [25]. SCS is comprised of 12 items on a 5-point scale, and there are two items applicable to each of the following aspects of “self-kindness,” “self-judgement,” “common humanity,” “isolation,” “mindfulness,” and “over-identification,” and six-scaled scores are obtained by totaling the answers. The higher the score, the higher the level of self-compassion. In case of missing responses, if more than half of the items are answered, the missing data are supplemented by averaging the answered items.

The QOL of the primary caregiver is measured each time at T1–T3 using the SF-8 [26]. SF8 is an 8-item, 5–6-point scale, with scores calculated based on a distribution of 50 points as the standard value using a unique scoring algorithm. Missing data are also handled using this scoring algorithm. The higher the score, the higher the health-related QOL.

In addition to these outcomes, the following questions are asked about basic attributes. At T1, the participants are asked about their relationship (from the child’s perspective), age (in 10-year increments), marital status, cohabitation status with partner, highest level of education, occupation, household income, and family members living in the same household. At T1, the following questions are asked about the child’s attributes: gender, age, name of the diagnosis, age at diagnosis, school attendance history, condition of disability, and required care. At T2 and T3, the respondents are asked if there are any changes in these circumstances and are asked to provide details if there are any. To ensure that the responses are not compulsory, the respondents are given the option of, “No response” and the online survey system is arranged so that respondents could progress to the next page without answering some or all questions.

The respondents are asked the following questions in the questionnaire to evaluate the process after attending the program and four weeks later: How did you feel after attending the program? Did you tell your family about the content of the program and the information you learned? Would you recommend the program to your friends? How can the program be expanded? They are asked their opinion about the program (age of their child when they attended the program, number of sessions, days the sessions are held, the length of the program, and the necessity of childcare).

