The mental health of mothers raising children with disabilities is related to their empowerment. Previous research has shown that depressive symptoms are associated with lower empowerment among mothers raising children with disabilities [8]. Also, mothers raising children with developmental disabilities participated in health-promoting activities infrequently; moreover, depressive symptoms, maternal empowerment, and two indicators of child-related QoL explained significant variance in healthy behaviors [9]. Parents often face a variety of difficulties in raising children with disabilities. Therefore, these parents need to be able to not only receive social resources including healthcare services but also use and coordinate social resources that are necessary for their children and families. In addition, these parents need the skills to cope with child- and family-related problems.

In a previous study, we conducted in-depth interviews with 34 families with children with severe disabilities who lived at home (mother, father, and siblings aged 12 years and older) [10] and conducted a questionnaire survey of 158 nurses and government officials using the Delphi method [11] to comprehensively list the factors that comprise the family empowerment model. Thereafter, we issued a self-administered questionnaire based on that model to 1659 families nationwide with children with severe disabilities who were living at home, to develop and verify the family empowerment model [12]. This research undertaken with family caregivers has shown an association between the empowerment and knowledge of social resources and how to use these resources in order to reduce burden. However, the above were observational studies. In this study, we verify, through implementational research, whether an intervention for each of these factors (specifically, by working on increasing the “self-reported capability to use social resources” and reducing the “caregiver burden”) can actually increase family empowerment. Furthermore, we aim to determine which of the three levels of Koren et al.’s conceptual framework (“family [internal] FA”, “service system SS,” and “community SP”) are actually empowered by this intervention.

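### The only social-resources item measured at baseline asks about capability but offers answers on frequency of use, so a change on it cannot be cleanly read as a change in capability

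*Protocol article*

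**What the plan says.** The Main outcome section of the protocol article lists the construct: "Secondary outcomes are caregiver burden, self-reported capability to use social resources, self-compassion, and QOL of primary caregivers". The Abstract, Background, Purpose, Data collection method and Data analysis sections use the same capability label. The Background makes it one of two factors through which the program is meant to raise empowerment, "by working on increasing the “self-reported capability to use social resources” and reducing the “caregiver burden".

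The Main outcome section then describes the measurement:

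- Source: "Two original items are created regarding the use of social resources based on discussions among the researchers in our previous study".
- Item 1, stem and timing: "The first question is asked each time at T1–T3: “Do you feel you can use social resources, properly".
- Item 1, answers: "respondents can select from “I often use social resources,” “I sometimes use social resources,” “I do not use social resources very often", and a fourth option for never using them.
- Item 2, asked at T2 and T3 only: "Do you feel that you are now more able to properly use social resources compared to when you answered the previous questionnaire".
- Item 2, answers: "can no longer use social resources,” “cannot use social resources very much,” “unchanged,” “can use social resources slightly more,” or “can use social resources very", the last option ending in the word often.
- Separately, the survey records "actual use of social resources (actual use volume and frequency) as basic attributes".

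The Data analysis section plans an ANCOVA for each secondary outcome at T2, in the same manner as the primary analysis, which adjusts for the T1 score. It also plans paired t tests of T1 against T3 in the early group and of T2 against T3 in the delayed group. It does not say which of the two items, or what combination, is the outcome.

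**The concern.** The label and the stem of item 1 are about being able to use resources; the answers are about how often they are used. The two can part company. A caregiver may come to feel able to arrange services yet need few, or may not have had time to obtain them. Another may use services heavily with little sense of using them properly.

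The timing makes this relevant. T2 falls within a week of the early group's fourth session, when confidence may have moved but service use may not have. The Data analysis section uses the T2 comparison to judge whether something the program addresses directly has improved. If item 1 supplies that comparison, a null result could reflect the answer scale, and a positive result could reflect use and be reported as capability.

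**Working it through.** No figure in the plan is at issue and no arithmetic applies. The check sets construct, stem, answers and planned analyses side by side.

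**Step 1: stem against answers.**

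| | Item 1 | Item 2 |
|---|---|---|
| Asked at | T1, T2, T3 | T2, T3 |
| Stem | feels able to use resources properly | more able than at the previous questionnaire |
| Answers | four grades of frequency (often, sometimes, not very often, never) | five options, mostly can or cannot |
| Match | none of the four options expresses capability | largely matches, with mixed anchors |

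**Step 2: does the protocol treat use and capability as the same thing?** No. Volume and frequency of actual use are collected as basic attributes, apart from the outcome. By the protocol's own classification, frequency of use is not the outcome it names.

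**Step 3: which item can enter the planned analyses?**

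| Planned analysis | Values needed | Item 1 | Item 2 |
|---|---|---|---|
| ANCOVA at T2, T1 score as covariate | T1, T2 | yes | no, no T1 value |
| Early group, paired t test | T1, T3 | yes | no, no T1 value |
| Delayed group, paired t test | T2, T3 | yes | both values exist, but each rates change over a different interval (T1–T2, then T2–T3), so their difference is not a change in capability |

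The planned analyses therefore point to item 1, although the article does not say so. The item with the mismatch is the one that the stated methods can use.

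**Step 4: what can a score on item 1 mean?** A respondent guided by the stem may use the options as rough grades of capability. A respondent guided by the options reports frequency. The article gives no way to tell which, so a group difference on item 1 is a mixture of the two in unknown proportion.

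**Step 5: is item 2 sound as a fallback?** Mostly. At T2 its reference point is the T1 questionnaire in both groups. By then the early group has completed the program and the delayed group has not started it. A direct comparison of the groups at T2 is therefore meaningful without a baseline value. Its weakness is in the anchors: not being able to use resources very much, and being able to use them very often, read as levels, whereas the middle option and the slightly-more option are changes.

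**The case against.** **The printed wording may be a translation.** The eligibility criteria exclude people who cannot read or write Japanese, so the questionnaire was presumably fielded in Japanese and the English options may not match it. Item 2 supports this caution: its top option says very often where one would expect much more. This stands, and it is why the first step of the fix is to check the fielded text.

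**Item 2 asks about capability.** A reader might infer from item 1 that a gain in capability goes unscored altogether. The documents do not support that: item 2 asks directly about such a gain at T2 and T3. What remains is that item 2 does not fit the T1-adjusted ANCOVA or the T1–T3 test.

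**Respondents need not answer by frequency.** A reader might infer that the score simply is frequency of use. The stem asks about capability, and actual use is asked elsewhere in the survey, so some respondents will answer in the spirit of the stem. This also stands; the sound claim is that the meaning is mixed.

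**The item 2 anchors are a lesser fault.** A family that was unable and remains so has a natural answer, unchanged, because the stem asks for a comparison. That is fair. The level-like anchors invite inconsistent answers but do not make the item unusable.

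**The stakes are limited.** Feasibility is the primary outcome, total FES at T2 is the main efficacy measure, and no decision rule turns on this item. The Discussion also counts better use of social resources among the hoped-for results, so a shift in use would be of interest. All true, but use is not the outcome that the protocol names and proposes to test.

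**Conclusion.** The point holds in a limited form. All four printed answers to item 1 grade frequency of use under a capability stem. Item 1 is the only social-resources item with a T1 value, so the planned T2 ANCOVA and the early group's T1–T3 test can use only that item. A change on it cannot be cleanly reported as a change in capability, which the Background names as one of the two factors the program works on.

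The size is one secondary outcome in a feasibility study; the primary outcome and the FES comparison are unaffected. A reader might want to express the harm as lost power. The documents do not allow it: they give neither the share of respondents who would follow the options over the stem nor an effect size for this item, and any figure would rest on invented inputs.

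The conclusion assumes that the English options reflect what was fielded, and that analysing secondary outcomes in the same manner as the primary one means adjusting for the T1 value. If the Japanese options concern capability, only the published text needs correcting.

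**What to change.** 1. Check the Japanese wording fielded for both items. If item 1's answers are about capability, correct the English text and stop there on item 1.
2. If they are about frequency and T1 has not been fielded, replace them with grades of being able to use resources properly (for example very well, fairly well, not very well, not at all). Word all five anchors of item 2 as changes, from much less able to much more able.
3. If T1 has been fielded, keep item 1 unchanged across T1 to T3, because rewording it partway would break the T1-adjusted comparison. Report it as self-reported frequency of use. Base any statement about capability on item 2, compared between groups at T2 without a T1 covariate, and note its mixed anchors as a limitation.
4. In every case, state in the Data analysis section which item supports which claim.

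The cost is a wording change to two questionnaire items or, after fielding, a narrower claim for one secondary outcome. No change to sample size or schedule is needed. The article does not say that these items were used in the earlier national survey, so a loss of comparability with it cannot be assumed.
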